## Abstract

**Introduction:**

The treatment of displaced, extra-articular fractures of the distal tibia remains controversial. These injuries are difficult to manage due to limited soft tissue cover, poor vascularity of the area and proximity to the ankle joint. Surgical treatment options are expanding and include locked intramedullary nails, plate and screw fixation and external fixator systems. The nail and plate options are most commonly used in the UK, but controversy exists over which treatment is most clinically and cost-effective. In this multicentre randomised controlled trial we aim to assess ratings of disability 6 months postinjury in patients who have sustained a distal tibia fracture treated with either an intramedullary nail or plate and locking screw fixation.

**Methods and analysis:**

Adult patients presenting at trial centres with an acute fracture of the distal tibia will be considered for inclusion. A total of 320 patients will provide 90% power to detect a difference of 8 points in Disability Rating Index (DRI) score at 6 months at the 5% level. The randomisation sequence is stratified by trial centre and age, and administered via web-based service with 1:1 treatment allocation. Baseline demographic and pre-injury functional data and radiographs will be collected using the DRI, Olerud and Molander, and EuroQol EQ-5D questionnaire. Clinical assessment, early complications and radiographs will be recorded at 6–8 weeks. Functional outcome, health-related quality of life and resource use will be collected at 3, 6 and 12 months postoperatively. The main analysis will investigate differences in DRI 6 months postsurgery, between the two treatment groups, on an intention-to-treat basis. Tests will be two-sided and considered to provide evidence for a significant difference if p values are <0.05.

**Ethics and dissemination:**

NRES Committee West-Midlands, 6/11/2012 (ref:12/WM/0340). The results of the trial will be disseminated via peer-reviewed publications and presentations at relevant conferences.

**Trial registration number:**

ISRCTN99771224.

Strengths and limitations of this studyThis will be the first multicentre randomised trial to assess the clinical and cost-effectiveness of intramedullary nail versus plate and locking screw fixation for patients with an extra-articular fracture of the distal tibia.Methodological qualities of the trial include: large number of intervention sites, optimised protocol to reduce risk of bias, appropriate sample size calculation and planned intention-to-treat analysis.The challenge for this study will be a potential lack of equipoise among trauma surgeons with regard to the treatment of this complicated type of fracture.

## Background

The tibia is the most commonly broken major bone in the leg. Injuries usually require hospital admission and frequently require surgery, resulting in prolonged periods (months) away from work and social activities.

The treatment of displaced, extra-articular fractures of the distal tibia (lower third) remains controversial. These injuries are difficult to manage due to the limited soft tissue cover, poor vascularity of the area and proximity of the fracture to the ankle joint. Infections, non-union and mal-union, are well-recognised complications.

Non-operative treatment is one option and avoids the risks associated with surgery. Sarmiento *et al*,^1^ in 2003, reviewed 450 closed fractures of the distal tibial following functional bracing: 13.1% developed a mal-union (defined as >7° of angulation or 12 mm shortening). A further study using a more robust definition of 10 mm shortening and 5° angulation found a higher rate of mal-union (26.4%).^2^ Bostman *et al*^2^ treated patients using a long leg cast and failure to maintain reduction led to surgical treatment with an intramedullary nail. Thirty-two of 103 cases required nailing at a mean of 9 days following injury. Two patients in this group and three in the non-operative group went on to have a non-union.^2^ Union rates were faster with intramedullary nailing compared with conservative treatment—median values were 12.5 and 14.5 weeks, respectively (p<0.001).^2^ Digby *et al*^3^ also found that non-operative treatment for tibial fractures in the metaphyseal region leads to unacceptable deformity and ankle stiffness. Therefore, non-operative treatment is not the treatment of choice in the majority of patients with a fracture of the distal tibia.

Surgical treatment options are expanding and include locked intramedullary nails, plate and screw fixation, as well as external fixator systems including the Ilizarov frame and hybrid fixators. External fixators may be beneficial in selected cases—particularly those with severe soft tissue injuries—but, in the UK, the nail and plate options are most commonly used for extra-articular fractures. Mid-shaft fractures of the tibia are generally successfully treated with locked intramedullary nails. However, in the more distal metaphyseal region of the tibia, the fixation may be less stable.^4^ The nail or screws that are inserted into the nail may break,^5^ mal-alignment may occur,^6^ and there is a risk that the nail will penetrate into the ankle joint.^7^
^8^

The development of ‘locking’ plates (where a thread on the head of the screws locks into the holes in the plate to create a ‘fixed-angle’ construct) has led to a recent increase in the use of plate fixation. However, plates are not without risks, they require greater soft tissue dissection, which carries a risk of infection, wound breakdown and devitalisation of the surrounding tissue.^9^

In a retrospective study of 111 patients with extra-articular fractures of the distal tibia (4–11 cm proximal to the plafond), a comparison was made between intramedullary nailing and plate fixation. Seventy-six fractures were treated with an intramedullary nail and 37 were treated with a medial plate.^10^ Nine patients (12%) had a delayed union or non-union in the intramedullary nail group and one patient (2.7%) had a non-union after plate fixation (p=0.10). Angular mal-alignment of ≥5° occurred in 22 patients with nails (29%) and 2 with plates (5.4%, p=0.003). The authors concluded that fractures of the distal tibia may be treated successfully with plates or nails, but that delayed union, mal-union and secondary procedures were more frequent after intramedullary nailing. Janssen *et al*^11^ found similar results, delayed union was higher in the intramedullary nail group (25%) compared to the plate fixation group (16.7%), rotational mal-alignment was also higher in the intramedullary nailing group (16.7%) compared with 0% in the plate group. However, this was not a randomised controlled trial (RCT) and the results do need to be interpreted with some caution. Randomised prospective assessment will be necessary to further clarify these issues and provide information about costs associated with these fractures.^10^

Only two prospective RCTs have been published to date. In the first, 64 patients were randomised either to intramedullary nail or plate fixation, for the treatment of a closed extra-articular fracture.^12^ The time to union was found to be similar for the two groups, and there was no difference in terms of Olerud and Molander Ankle Score (OMAS) at 2 years. However, a significant difference was observed in the number of wound complications: one in the intramedullary nail group versus seven in the plate group. This paper concludes that intramedullary nailing is the treatment of choice for this injury. However, the method of randomisation was poorly described and so bias in group assignment may have occurred. The study used traditional (non-‘locking’ plates) rather than the newer fixed-angle devices. Furthermore, the study included patients with Tschene classification C2 soft tissue injuries, which may have influenced the results. The second trial randomised 111 patients either to intermedullary nail fixation or ‘locking’ plate fixation.^13^ This trial also showed no difference in the time to union but, 1 year after the injury, there was some evidence of improved American Orthopaedic Foot and Ankle Society functional scores in the nail group. However, this was a single-centre investigation and over 20% of the patients in the trial were lost to follow-up.

In a meta-analysis, Zelle *et al*^14^ reviewed 1125 extra-articular fractures of the distal tibia. They reported that non-union, mal-union and infection rates were similar for patients undergoing intramedullary nailing and plate fixation. It must be noted that none of the studies in the review were RCTs.

## Pre-pilot data

We performed a pilot study involving 24 patients with extra-articular fractures of the distal tibia that were closed, or Gustilo and Anderson grade 1.^15^ The study was a RCT with clinical assessment, functional outcomes and radiological images performed at baseline, 6 weeks, and 3, 6 and 12 months postsurgery. The study was performed to obtain an estimate of the potential effect size to inform the sample size calculation for a larger definitive trial, and to assess recruitment rates and study feasibility.

The study had 12 patients in each group. There was no statistically significant difference between the groups 6 months after the injury but there was a 10-point difference (SD 20) in the Disability Rating Index (DRI)^16^ in favour of the intramedullary nail group. More secondary procedures were required in the ‘locking’ plate fixation group. There was also a large difference in the cost of the implants.

This pilot study provides compelling evidence to support the development of a definitive RCT in multiple centres.

## Trial design

The trial will be carried out in accordance with Medical Research Council Good Clinical Practice^17^ and applicable UK legislation, using the following protocol. The trial will be reported in line with the CONSORT statement.^18^

## Null hypothesis

There is no difference in the DRI at 6 months after injury between adults with a displaced fracture of the distal tibia treated with ‘locking’ plate fixation versus intramedullary nail fixation.

## Objectives

The primary objective is:
 To quantify and draw inferences on observed differences in the DRI between the trial treatment groups at 6 months after injury.

The secondary objectives are:
To quantify and draw inferences on observed differences in early functional status at 3 months and later functional status at 12 months.To quantify and draw inferences on observed differences in the radiological outcomes: non-union, mal-alignment and shortening.To identify any differences in health-related quality of life between the trial treatment groups in the first year after injury.To determine the complication rate of intramedullary nail fixation versus ‘locking’ plate fixation in the first year after injury.To investigate, using appropriate statistical and economic analytical methods, the resource-use, costs and comparative cost-effectiveness of intramedullary nail fixation versus ‘locking’ plate fixation.

## Trial summary

The proposed project is a two-phased study. Phase 1 (internal pilot) will determine the expected rate of recruitment in a large-scale multicentre RCT in this complicated area of trauma research. Phase 2 (main phase) will be the proposed RCT in a minimum of 18 trauma centres across the UK.

### Internal pilot summary

The pilot will take place in six centres over a period of 6 months. The main aim of this initial phase will be to determine the number of eligible and recruited patients in the trauma centres over the course of 6 months. Screening logs will be kept at each site to determine the number of patients assessed for eligibility and reasons for any exclusion. In addition, the number of eligible and recruited patients, and the number of patients who decline consent/withdraw, will be recorded.

#### Main RCT summary

All adult patients presenting at the trial centres with an acute fracture of the distal tibia are potentially eligible to take part in the trial. The broad eligibility criteria will ensure that the results of the study can readily be generalised to the wider patient population. A computer-generated randomisation sequence, stratified by centre and age, will be produced and administered independently by a secure web-based service. Randomisation will be on a 1:1 basis to either intramedullary nailing or ‘locking’ plate fixation. Both of these operations are widely used within the NHS and all of the surgeons in the chosen centres will be familiar with both techniques.

Baseline demographic data, radiographs and pre-injury functional data using the DRI and the OMAS Questionnaire will be collected. The patients will also be asked to fill out the EuroQol EQ-5D health-related quality-of-life questionnaire twice at baseline; once to indicate their typical preinjury health status and a second time to indicate their current ‘postinjury’ status.

A research associate will perform a clinical assessment and record any early complications at 6 weeks, and a radiograph will be taken. A further clinical assessment and radiograph will also be taken at 12 months postoperatively to detect late complications. Functional outcome, health-related quality of life and resource-use questionnaires will be collected at 3 months, 6 months and 12 months postoperatively.

## Outcome measures

The primary outcome measure for this study is the *DRI*.^16^ The DRI score is a validated questionnaire that is self-reported (filled out by the patient). It consists of 12 items specifically related to function of the lower limb. This data will be collected at baseline, 3, 6 and 12 months postoperatively (table 1). The DRI has been proven to be a robust and practical clinical and research instrument, with good responsiveness and acceptability for assessment of disability caused by impairment in the lower limb.

**Table 1 BMJOPEN2015009162TB1:** Follow-up measures

Time point data collection	
Baseline	DRI, OMAS, EQ-5D *preinjury*, *EQ-5D current* and radiographs
6 weeks	Complication records, radiographs and operative record
3 months	DRI, OMAS, EQ-5D, record of complications/rehabilitation or other interventions and resource-use questionnaire
6 months	DRI, OMAS, EQ-5D, record of complications/rehabilitation or other interventions and resource-use questionnaire
12 months	DRI, OMAS, EQ-5D, radiographs, record of complications/rehabilitation or other interventions and resource-use questionnaire

DRI, Disability Rating Index; OMAS, Olerud and Molander Ankle Score.

The secondary outcome measures in this trial:

*OMAS* is a self-administered patient questionnaire. It is a good outcome tool for assessing symptoms after an ankle fracture. The score is based on nine different items: pain, stiffness, swelling, stair climbing, running, jumping, squatting, supports and work/activities of daily living.^19^ The scoring system correlates well with parameters considered to summarise the results after this type of injury and is therefore recommended for use in scientific investigations.

*EQ-5D* is a validated, generic health-related quality-of-life measure consisting of five dimensions, each with a 3-level answer possibility. Each combination of answers can be converted into a health utility score.^20^ It has good test–retest reliability, is simple for patients to use and gives a single preference-based index value for health status that can be used for broader cost-effectiveness comparative purposes.

*Complications*: All complications will be recorded, including mal-union, delayed/non-union, infection, wound complications, vascular and neurological injury, and venous thromboembolism. A record will also be kept of any other surgery required in relation to the index fracture, including removal of any metalwork.

*Radiographic evaluation*: Standard anteroposterior and lateral radiographs of the tibia and fibula will be taken at baseline, 6 weeks and 12 months after the injury. If a radiograph is not taken at 12 months, say for example, the fracture has been considered by the treating surgeon to be healed at an earlier time point, the last radiograph taken before 12 months will be collected. These are radiographs routinely used for the investigation of patients with a suspected fracture of the distal tibia and for the follow-up of such patients following any intervention, so there will be no need to request any additional or special investigations.

We will use techniques common in long-term cohort studies to ensure minimum loss to follow-up, such as collection of multiple contact addresses and telephone numbers, mobile telephone numbers and email addresses. Considerable efforts will be made by the trial team to keep in touch with patients throughout the trial by means of newsletters, etc.

## Sample size

The minimum clinically important difference (MCID) is eight points on the primary outcome (DRI) measurement scale. The DRI is a 12-question, patient reported, functional outcome measure (physical exercise or sports, running, heavy physical work, heavy lifting, carrying a bag, leaning over a wash-stand, making a bed, moderate physical work, walks, mounting stairs, sitting still more than briefly and dressing or undressing) converted to a 100-point scale where ‘0’ represents normal function and ‘100’ represents complete disability. At an individual patient level, a difference of eight points represents the ability to climb stairs or run, with ‘some difficulty’ versus with ‘great difficulty’. At a population level, eight points represents the difference between a ‘healthy patient’ and a ‘patient with a minor disability’. Eight points also corresponds approximately to the clinically worthwhile benefit identified in other studies and the difference between treatment group means in our pilot study.

The SD of the DRI in our pilot study was approximately 20 points; the sample size has also been estimated for a larger and smaller SD to obtain an indication of the sensitivity to changes in this parameter. Assuming the distribution of DRI in the study populations to be approximately normal, which is consistent with assumptions made for other reported trials using DRI as the primary outcome measure, table 2 shows the total trial sample size with two-sided significance set at 5% for various scenarios of power and sample SD.

**Table 2 BMJOPEN2015009162TB2:** Sample size at variable power and SD

	Power	
SD	80%	90%
15	112	150
20	198	**264**
25	308	412

Bold typeface indicates the actual sample size chosen for this trial.

The bold figure of 264 patients represents the most likely scenario, based on our current knowledge, for 90% power to detect the selected MCID. Allowing a margin of 20% loss during follow-up, this gives a figure of *320 patients in total*. Therefore, 160 patients randomised to each group will provide 90% power to detect a difference of eight points in DRI at 6 months with 90% power at the 5% level.

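### 264 evaluable patients, 20% loss, 320 randomised and 90% power cannot all hold: 320 covers 17.5% loss, and at 20% loss power is about 89% (minor)

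*Protocol article*

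**What the plan says.** The Sample size section sets the target difference: "The minimum clinically important difference (MCID) is eight points on the primary outcome (DRI) measurement scale". It takes its variability from the pilot: "The SD of the DRI in our pilot study was approximately 20 points". For the test level and the scenarios, it says that "table 2 shows the total trial sample size with two-sided significance set at 5% for various scenarios of power and sample SD". The entry chosen from that table is 264 in total, which the section describes as the likeliest scenario "for 90% power to detect the selected MCID".

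The loss allowance follows: "Allowing a margin of 20% loss during follow-up, this gives a figure of" 320 in total. The section then concludes that "160 patients randomised to each group will provide 90% power to detect a difference of eight points in DRI at 6 months". Allocation is equal (Main RCT summary: "Randomisation will be on a 1:1 basis to either intramedullary nailing").

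The abstract gives the total and the power but no loss rate: "A total of 320 patients will provide 90% power to detect a difference of 8 points".

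**The concern.** Loss to follow-up is a fraction of the patients randomised. If 264 must remain after 20% are lost, the number randomised has to be 264 divided by 0.8. The protocol's 320 is smaller than that, so the section makes four statements (264 needed, 20% lost, 320 randomised, 90% power) of which at most three can be true together.

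What is at stake is the accuracy of a headline design figure. A reader of the Sample size section will take 20% as the loss the trial can bear at 90% power, and it is not. Loss of this order is not remote either: the Background faults an earlier randomised trial of nail against locking plate for losing over 20% of its patients.

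**Working it through.** **Inputs.** Difference 8 points, SD 20, two-sided 5%, power 90%, evaluable total 264, loss 20% and randomised total 320 are all from Sample size. Equal allocation is from Main RCT summary. The main comparison is an unadjusted Student t test at 6 months (Statistical analysis).

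**Step 1: reproduce the protocol's 264.** With the normal approximation, n per arm = 2(z₀.₉₇₅ + z₀.₉₀)² SD² / difference²
= 2 x (1.960 + 1.2816)² x 20² / 8² = 131.3, rounded up to 132 per arm, 264 in total. This matches exactly. The exact t-based calculation gives 266.

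**Step 2: apply the loss allowance.**
- Dividing by the retained fraction: 264 / 0.80 = 330 (165 per arm).
- Adding 20% to the evaluable number: 264 x 1.2 = 316.8, which rounds up to 320.
- Starting from 266 does not rescue the figure: 266 / 0.80 = 332.5, so 333.

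The stated 320 fits the second line and not the first. It is 330 - 320 = 10 patients short, or 10/320 = 3.1%.

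**Step 3: what 320 delivers.**
- Evaluable after 20% loss: 320 x 0.80 = 256 (128 per arm), 264 - 256 = 8 below target.
- Largest loss that still leaves 264: 1 - 264/320 = 17.5%, i.e. 56 patients, where 20% would be 64.

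**Step 4: power.** With 128 per arm, the standardised difference is 8 / (20 x √(2/128)) = 8 / (20 x 0.125) = 3.20. Normal-approximation power is Φ(3.20 - 1.96) = Φ(1.24) = 89.3%. The t-test figures come from the noncentral t distribution.

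| Evaluable total | Normal approximation | t test |
|---|---|---|
| 256 (320 with 20% loss) | 89.3% | 89.0% |
| 264 (320 with 17.5% loss) | 90.1% | 89.9% |
| 320 (no loss) | 94.7% | 94.6% |

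Compared like for like, the inflation step costs about 0.9 point: 90.14 - 89.25 = 0.89 by the normal approximation, and 89.93 - 89.03 = 0.90 by the t test. Setting the t-test 89.0% against a nominal 90% would overstate it slightly, because 264 itself gives 89.9% on that basis.

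**The case against.** The strongest defence is that the effect is smaller than the precision of the inputs. By the normal formula, 128 per arm still gives 90% power if the SD is 8 / (3.2415 x 0.125) = 19.74, or if the difference is 3.2415 x 20 x 0.125 = 8.10 points. The protocol describes the SD only as about 20, from a 24-patient pilot, and a value of 19.7 would be reported the same way. Its own Table 2 moves from 264 to 412 when the SD is 25. All of this stands, and it is why the point is minor. It does not make the four figures agree.

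A second defence is that a 20% margin may mean adding 20% to the evaluable number. No formula is printed, so the multiplication by 1.2 is an inference. But the sentence describes the 20% as loss during follow-up. If an add-on was intended, the loss actually covered is 17.5%, and the text still needs to say so.

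A reader might also infer three stronger things that the protocol does not support:
- **That the abstract is wrong.** It gives no loss rate, and its power statement is true for any loss up to 17.5%.
- **That a monitoring committee would judge retention against a wrong limit.** The protocol sets no retention limit or trigger. Its one stated progression criterion is the recruitment rate.
- **That covariate adjustment makes up the shortfall.** The main analysis is the unadjusted t test. Regression on age and gender is additional, and no covariate-outcome correlation is given from which a gain could be calculated.

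**Conclusion.** Wrong as written in the Sample size section, and minor. With 320 randomised, either the loss allowance is 17.5% at 90% power, or the power is about 89% at 20% loss. The gap is 8 evaluable patients, 10 randomised patients (3%) and about 0.9 point of power.

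This rests on the protocol's own inputs (8 points, SD 20, two-sided 5%, equal arms), on loss being shared equally between the arms, and on reading the 20% as a share of those randomised. It does not show that the trial is materially underpowered; a departure of the SD from 20 would matter far more.

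**What to change.** Keep 320 and restate the sentence in the Sample size section, for example: a total of 320 patients (160 per group) allows for 17.5% loss to follow-up, leaving 264 evaluable patients and 90% power; if 20% are lost, 256 are evaluable and power is about 89%.

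The abstract needs no change on this account. The cost is a text correction: the stated figure becomes slightly less favourable, and neither the design, the analysis nor the recruitment target changes.
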